
### Study intervention

2.7

Following recruitment for surgical treatment, a multidisciplinary team will define the optimal therapeutic approach taking into account patient-related factors (e.g., age, past medical history, and comorbidities) as well as tumor-specific characteristics (e.g., histology, size, and anatomical location). The team will also consider the eventual addition of radiotherapy and/or chemotherapy before or after the surgery as neoadjuvant or adjuvant therapies, respectively: the use of brachytherapy is not planned in the study. Subsequently, the patients will undergo STS radical resection to obtain negative margin classified as R0 in accordance with the guidelines of the Union for International Cancer Control Hermanek and Wittekind (23) and a reconstructive plastic surgery recovering the soft tissue defects.

Afterwards, at the rehabilitation center, all patients will undergo the same (i.e., no randomization) rehabilitation treatment consisting of postural steps, bed–wheelchair transfers, verticalization, ambulation without weight bearing on the operated limb or with partial bearing and ambulation with gradual weight bearing with or without aid Galluccio et al. (24).

The rehabilitative intervention will include two 50-minute sessions per day, six days per week for a total duration of approximately 60 days and it will imply both a robotic and conventional treatment.

As for the former, the recover of muscular strength, balance, proprioception and lower limb joints range of motion will be pursued using one or more of the following rehabilitative robots:

G-EO System (Reha Technology, Olten, CH): end-effector robot characterized by a body weight support and two footplates placed on a double crank and a rocker gear system, inducing locomotor gait pattern;Lambda (Lambda Health System, Yverdon-les-Bains, CH): end-effector robot for rehabilitation of patients with lower limb neuromotor disabilities. The patient sits in a chair and is secured distally by two footplates supporting single and multi-joint movements in passive, assisted or active mode;Walker View (TecnoBody, Dalmine, IT): an auto-adaptive instrumented treadmill. The robot will support the patients’ body weight and will adapt the speed according to the patient’s residual motor capabilities. In addition, the patient will be immersed in a virtual reality environment that could enhance the engagement during the session;Hunova (Movendo Technology, Genova, IT): a stabilometric platform training the patients’ equilibrium and posture in a sitting or standing position.

In accordance with Italian standards on inpatient rehabilitation, the proposed approach will not be limited to robotic treatment but will also incorporate traditional one where the motor exercises will be performed or assisted by physical therapists, mostly in one-to-one sessions.

As reported in **Figure 1**, the following four evaluation sessions will be planned throughout the duration of the study:

*T_0_* (within 7 days before surgery): an analysis of the patient’s demographic and clinical characteristics will be carried out in order to define the most suitable surgical approach. Then, a clinical survey composed of MSTS-LL, TESS-LL, NRS, BPI, DN4, LANSS, SF-36, and EORTC-QLQ-C30 will be adopted to evaluate the patient functional impairments, activity limitations during daily activities, pain and QoL at the beginning of the study;*T_1_* (within 7 days post-surgery): the aforementioned clinical survey will be submitted to the patient to evaluate the surgery’s short-term effects on functional impairments, activity limitations during daily activities, pain, and QoL;*T_2_* (within 30 days post-surgery): the clinical survey will be submitted to the patients to evaluate the clinical status before the beginning of the rehabilitation treatment. Moreover, the patients’ ambulation capabilities during free overground walking will be analyzed as soon as the patient is able to walk. Gait analysis will be conducted using the optoelectronic, marker-based BTS Smart D 500 system (BTS Bioengineering, Milan, Italy) within a calibrated acquisition volume of 5 × 3 × 2 m³. Before to each session, eight cameras will be mounted on tripods and geometrically calibrated; twenty-two 10-mm photo-reflective markers will be positioned on specific anatomical landmarks according to the Davis protocol Davis III et al. (25). Kinematic data will be acquired at a sampling frequency of 100 Hz. Kinetic parameters will be collected through two P-6000 force platforms (BTS Bioengineering, Milan, Italy) at a sampling rate of 1000 Hz. Surface electromyography will be recorded using eight FREEEMG sensors (BTS Bioengineering, Milan, Italy) applied to the following muscles of the operated limb: 1) Rectus Femoris responsible for hip flexion and knee extension, 2) Vastus Lateralis responsible for hip flexion and knee extension, 3) Vastus Medialis responsible for hip flexion and knee extension, 4) Biceps Femoris responsible for hip extension and knee flexion, 5) Semitendinosus responsible for hip extension and knee flexion, 6) Gluteus Maximus responsible for hip extension, 7) Tibialis Anterior responsible for ankle flexion, 8) Gastrocnemius Lateralis responsible for ankle extension. These muscles were selected because they are superficial and play a primary role in physiological gait Barbero et al. (26). Electrode placement will follow the recommendations of the Surface EMG for the Non-Invasive Assessment of Muscles guidelines Hermens et al. (27). Myoelectric signals will be sampled at 1000 Hz. Whether access to the anatomical landmarks or muscle bellies is limited due to wound healing, medical dressings or other clinical constraints, alternative strategies will be considered based on the patient’s condition and the requirement for accurate measurement. The markers may be positioned over bandages when necessary, and EMG sensors may be placed as close as possible to the target muscle belly while respecting clinical safety and feasibility. During each session, the patients will complete ten barefoot walking trials at a self-selected speed along an 8.0 m straight walkway. When walking aids (e.g., unilateral crutch, cane, or walker) will be required, the same aid will be consistently used across all assessment sessions to ensure standardization of testing conditions;

• *T_3_*(within 90 days post-surgery): the evaluations carried out in the previous session will take place in order to assess the impact of the personalized rehabilitation treatment and of the entire study on patients clinical characteristics, motor performance, and QoL.

The first two evaluation sessions will be carried out at the surgical center, while the remaining ones will be held at the rehabilitation center.

### Intervention adherence

2.8

Since the patients will undergo surgical treatment, rehabilitation and eventually radiotherapy and/or chemotherapy during their inpatient stay across the two study centers, a high degree of adherence to the intervention is expected. To ensure both consistency and quality in the delivery of the rehabilitation program, adherence will be systematically monitored by an independent team of clinical professionals. This team will conduct periodic reviews of the treatment session logs to verify protocol compliance. In cases of deviations or risks of reduced adherence, corrective strategies will be implemented. Such strategies may include providing targeted refresher training sessions for the involved clinical staff, as well as delivering timely feedback to therapists to reinforce protocol fidelity and optimize patient engagement.

### Complementary and supportive therapies

2.9

In accordance with Italian standards for inpatient rehabilitation, the proposed program will not be limited to robotic technologies (i.e., the end-effector robots G-EO System and Lambda, the instrumented treadmill with body weight support Walker View and the stabilometric platform Hunova) but will also incorporate conventional physiotherapy methods. Each patient will follow an individualized treatment plan focusing on the lower limbs and trunk with the aim of facilitating postural transitions, improving balance, and restoring gait. The intervention will consist of daily sessions of approximately 50 minutes, administered five days per week, and continued throughout the entire study period.

All the conventional and robotic rehabilitative sessions will be daily recorded by the therapists.

### Outcome assessment

2.10

#### Primary endpoint

2.10.1

The primary endpoint of the study will be the improvement of TESS-LL score between *T_0_*(baseline) and *T_3_*(end of the rehabilitation treatment).

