### Study objectives

2.1

The main purpose of the study is to assess the effects of a personalized rehabilitation protocol on clinical status, motor performance, and quality of life in patients undergoing surgery for STS lower limbs.

To meet this objective, the following steps were planned:

Identification of clinical characteristics and motor damage after STS surgical removal;Impact of perioperative treatments and surgery on patients QoL;Impact of personalized post-operative rehabilitation treatment on patients clinical characteristics, motor performance and QoL.

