**Figure 1 f1:**
[figure not shown]
Standard Protocol Items: Recommendations for Interventional Trials (SPIRIT) schedule of enrollment, interventions and assessments. *T_0_* (within 7 days before surgery): baseline assessment; *T_1_* (within 7 days post-surgery): post-surgery assessment; *T_2_* (within 30 days post-surgery): pre-rehabilitation assessment; *T_3_* (within 90 days post-surgery): post-rehabilitation assessment.

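### The primary TESS-LL contrast runs from before surgery to after rehabilitation, so it nets the surgical loss against the gain and does not isolate the rehabilitation period that the main objective names

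*Protocol article*

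**What the plan says.** Section 2.1 of the protocol article sets the objective: "The main purpose of the study is to assess the effects of a personalized rehabilitation protocol on clinical status, motor performance, and quality of life". Section 2.10.1 sets the endpoint: "The primary endpoint of the study will be the improvement of TESS-LL score between" T0 and T3. Section 2.12.1 compares the TESS-LL scores at those two visits with a paired non-parametric test, calls a patient a responder if the score changes by more than 7 points, and carries responder status into logistic models for predictors of recovery.

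The legend of Figure 1 dates the visits. T0 is "within 7 days before surgery): baseline assessment", T2 is "within 30 days post-surgery): pre-rehabilitation assessment" and T3 is "within 90 days post-surgery): post-rehabilitation assessment". Section 2.7 includes TESS-LL in the clinical survey and repeats that survey at T2 "to evaluate the clinical status before the beginning of the rehabilitation treatment". Section 2.12.2 compares the gait data between T2 and T3. It compares the questionnaires over time by ANOVA or Friedman test, without naming a T2-to-T3 contrast.

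The Introduction says that these operations impair lower-limb function. Section 2.2 describes the study as uncontrolled. Section 2.5 sets 50 patients from case volume and calls the results exploratory.

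**The concern.** The interval from T0 to T3 contains resection, reconstruction, early healing, any adjuvant therapy and the rehabilitation programme. Surgery and rehabilitation are expected to move TESS-LL in opposite directions, and the primary contrast reports only their balance. A programme that exactly restores what surgery took away has an expected primary result of zero. A programme that restores most of it has a negative one.

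Three things are at stake. The first is the reading of the primary test against the stated purpose. The second is the responder label: a patient who regains all lost function shows no change from T0 and counts as a non-responder. The third is the predictor models, where an apparent predictor of recovery may partly reflect the extent of surgery or function before it. The article gives no reason for using the pre-surgical reference, and it words the endpoint as improvement, not as return to the pre-operative level.

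**Working it through.** **Plan's own figure.** There is no power calculation to reproduce: the 50 patients rest on case volume, and no effect size, SD or power is given.

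**Decomposition.** From the visit definitions alone,

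T3 − T0 = (T3 − T2) + (T2 − T0) = G − L,

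where G is the gain over the rehabilitation period and L is the loss from T0 to T2. The primary contrast is zero when G = L and negative when G < L, however large G is. This needs no outside number.

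**Inputs from the article.** n = 50 (section 2.5); significance level 0.05 (section 2.12.2), taken as two-sided; Wilcoxon signed-rank test and 7-point responder cut (section 2.12.1).

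**Assumptions.** SD 15 points at each visit and within-patient correlation 0.5, so the SD of a change is 15 × √(2 × (1 − 0.5)) = 15. G is fixed at 20 points. L is varied because the article gives no value.

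**Scale of the test.** The shift detectable with 80% power is about (1.96 + 0.84) × 15 / √50 = 5.9 points. For change SDs of 10 and 20 it is 4.0 and 7.9. A net difference of 10 points either way will usually be significant.

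**Results for T0-to-T3 (simulated Wilcoxon test).** Responder share = 1 − Φ((7 − (G − L)) / 15).

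| Loss L | Mean change G − L | Significant improvement | Significant worsening | Responders (>7) |
|---|---|---|---|---|
| 10 | +10 | about 99% | 0% | 58% |
| 20 | 0 | about 2-3% | about 2-3% | 32% |
| 25 | −5 | 0% | about 62% | 21% |
| 30 | −10 | 0% | about 99% | 13% |

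A normal approximation agrees. For L = 25, 5 / (15/√50) = 2.36 and Φ(2.36 − 1.96) = 0.65, slightly above the Wilcoxon figure, as expected. For L = 10 or 30, 10 / (15/√50) = 4.71 and Φ(4.71 − 1.96) = 0.997.

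**Same data, T2-to-T3.** The mean change is +20 in every row. The test is significant in about 100% of trials, and 1 − Φ((7 − 20)/15) = 81% of patients are responders, whatever L is.

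**Sensitivity to the SD of change.** With SD 10 and SD 20, L = 30 gives significant worsening in about 100% and 92% of trials, and L = 10 gives significant improvement in about 100% and 92%. With full restoration (G = L), 24% to 36% of patients still exceed the 7-point cut, through spread between patients alone.

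**The case against.** **Net recovery is a legitimate target.** Section 2.1 lists motor damage after tumour removal and the impact of surgery and perioperative treatment on quality of life among its steps. Section 2.7 says T3 serves to assess the rehabilitation and the study as a whole. T0-to-T3 fits that wider aim, so a reader who infers that the primary test cannot answer the study's question goes too far. What stands is narrower: the contrast does not isolate the rehabilitation period, which is the main purpose as written.

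**The loss may be small.** A reader might infer that the primary analysis will show no benefit, or harm. The documents do not support that. They expect a loss but give no size, and with a 10-point loss the planned test would succeed almost always. The defect is that the answer depends on L, not that it is bound to be unfavourable.

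**T2-to-T3 has its own confounding.** This stands in full. If healing alone added 10 points and rehabilitation nothing, T2-to-T3 would be significant in about 99% of trials under the same assumptions; with 7 points, in about 88%. The near-100% figure above shows that the contrast is unaffected by L; it does not show that rehabilitation works. The change of contrast removes a component of opposite sign and nothing more.

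**The damage is partly contained.** The results are called exploratory, TESS-LL is collected at T2, and change over time on the clinical scales is a secondary endpoint. The T2-to-T3 change can therefore be recovered, including for planning later trials. But no such questionnaire contrast is named, and the responder rule does not use T2.

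**Different centres.** The article says "The first two evaluation sessions will be carried out at the surgical center, while the remaining ones will be held at the rehabilitation center". One might infer a measurement difference between T0 and T3. Nothing indicates that the questionnaire is given differently at the two centres, so this adds little.

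**Conclusion.** The concern holds as a mismatch between the stated main purpose and the primary contrast, its test and the responder rule. The algebra follows from the article's own visit definitions and rests on no assumption. The size is illustrative only: with the same 20-point gain, the result moves from significant improvement in about 99% of trials to significant worsening in about 99% as the assumed surgical loss goes from 10 to 30 points, and the responder share falls from 58% to 13%. Those figures assume 50 analysed patients, a change SD of 15 and a two-sided 0.05 level; change SDs of 10 and 20 give the same pattern. Because this concerns the primary endpoint and the responder rule, it should be settled before analysis.

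**What to change.** **Preferred.** In sections 2.10.1 and 2.12.1, make the TESS-LL change from T2 to T3 the primary contrast and the basis of the responder rule. Keep T0-to-T3 as a named secondary endpoint, *recovery relative to pre-operative function*.

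**Alternative.** If T0-to-T3 stays primary, reword the primary objective in section 2.1 as net recovery against pre-operative function, say so in section 2.10.1 in place of improvement, and name T2-to-T3 as the key secondary contrast.

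**Either way.** Report T2-to-T3 as change over the rehabilitation period and state that, without a control group, it also contains natural healing and any adjuvant therapy.

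**Cost.** An amendment to the endpoint and analysis wording (and to the objective under the alternative), plus a registry update. No new visit or data are needed, because TESS-LL is already scheduled at T2.

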#### Secondary endpoint

2.10.2

The secondary endpoint of the study will be the improvement over time of the patient’s clinical status and trunk and lower limb biomechanics.

The former will be evaluated through the use of the presented clinical scales and patient-oriented questionnaires; the latter will be quantified through the aforementioned gait analysis. The parameters adopted to quantify the patients’ ambulation performance will be: *i)* the stance/swing phase, gait cycle duration, step length, stride length for both limb as well as the corresponding symmetry indices computed as described in Demofonti et al. (28). The step width, walking speed and cadence will also be evaluated regardless the limb side; *ii)* the trunk and both lower limb joints kinematics along the sagittal plane. Therefore the trunk, hip, knee and ankle flexion/extension will be evaluated and the related ranges of motion will be quantified; *iii)* the vGRF exerted on the ground by both limbs and the related peak values, loading rates and symmetry indices Demofonti et al. (28); *iv)* the myoelectric activity of the muscles of the operated limb and the related Root Mean Square values. The Co-Contraction Index values will be assessed for the agonist-antagonist muscle pairs RF/BF and TA/GL Infarinato et al. (29). The eventual presence of correlation between the gait indicators and the quality of life parameters will be evaluated.

During data analysis, the authors would consider a sub-group comparison on the basis of STS location (i.e., thigh anterior, medial or posterior compartment) or the resected muscles.

### Study withdrawal

2.11

The patients may withdraw from the study at any time, without penalty, and without the need to provide a justification. In such circumstances, no additional study procedures will be carried out, while data collected prior to withdrawal will be retained and analyzed in accordance with the study protocol.

Discontinuation may also occur at the discretion of the principal investigator. In this case, the reason for withdrawal will be duly documented and the investigator will be responsible for promptly informing the patient and arranging an appropriate clinical follow-up outside the study, consistent with standard medical practice.

In the event of a drop-out, a replacement patient will be enrolled, if necessary, in order to ensure the achievement of the planned sample size.

### Statistical analysis

2.12

A statistical analysis on outcomes measures will be conducted.

Descriptive statistics of the sample will include frequencies for categorical data, median and interquartile range for ordinal variables, and mean and standard deviation for continuous measures.

#### Primary analysis

2.12.1

The primary endpoint will be assessed by comparing the TESS-LL score at *T_0_*and *T_3_*using a non-parametric test for paired samples (e.g., Wilcoxon signed-rank test). In addition, the primary endpoint will be used to classify the patients as responders (a change in TESS-LL score greater than 7 points) or non-responders. Subsequently, baseline clinical data that will be significantly different between responders and non-responders will be adopted as inputs for multivariate logistic regression models aiming to investigate potential predictors of recovery.

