### Baseline assessment

2.6

Once the written informed consent is acquired, a baseline assessment will be conducted for each patient. Concerning patient’s demographic and clinical characteristics, the following data will be collected.

Demographics (e.g., age, gender, height, mass);Past medical history;Tumor site;Histopathological tumor characteristics;Tumor staging;Information on adjuvant and/or neoadjuvant therapies and surgery;Medications taken;Functional impairments evaluated through the Musculoskeletal Tumor Society Rating Scale differentiated for the Lower Limb (MSTS-LL) Enneking et al. (15). This scale includes six domains regarding pain, functions, emotional acceptance, use of an external aid, walking, and lifting capabilities: it provides a total score ranging from 0% to 100% with higher values indicating better functional status;Activity limitations evaluated through the Toronto Extremity Salvage Score differentiated for the Lower Limb (TESS-LL) Davis et al. (16). It contains 30 questions assessing how difficult daily activities are (e.g., mobility, working, and wearing) execution on a scale from 0 (i.e., impossible to perform) to 5 (i.e., no difficulty). The final score ranges from 0% to 100% with higher values indicating better function;Pain evaluated through the Numerical Rating Scale (NRS) Downie et al. (17) and the Brief Pain Inventory (BPI) Cleeland and Ryan (18). The former quantifies pain in adult with a score ranging from 0 (no pain) to 10 (worst pain imaginable), the latter assesses pain intensity and its interference with daily activities with a score ranging from 0 to 10 with higher values indicating more severe pain and greater functional impairment. In addition, the neuropathic pain will be evaluated through the Douleur Neuropathique en 4 Questions (DN4) Bouhassira et al. (19) and the Leeds Assessment of Neuropathic Symptoms and Signs (LANSS) Bennett (20). The former includes 10 items: seven are related to patient-reported symptoms (i.e., burning, painful cold, electric shocks, tingling, needles, numbness, and itching) and three to clinical examination (i.e., hypoesthesia to touch, hypoesthesia to pinprick and pain provoked by brushing). Each positive answer scores 1 point, with a total score ranging from 0 to 10: a score of 4 or higher is indicative of neuropathic pain. The latter allows the discrimination between the nociceptive pain and the neuropathic one, combining subjective questions regarding symptoms (e.g., burning sensations, tingling, electric shocks) and objective sensory tests (e.g., changes in sensitivity to touch or pinprick). It provides a total score ranging from 0 and 24 with a value greater than 12 indicating a significant neuropathic component to the pain. From a general perspective, the use of the NRS, BPI, DN4 and LANSS will allow a granular characterization of the patient’s pain, including intensity, impact on activities and qualitative sensory descriptors;The perceived QoL evaluated through the Short Form Health Survey 36 (SF-36) Ware Jr (21) and the European Organisation for Research and Treatment of Cancer Quality-of-Life Questionnaire (EORTC QLQ-C30) Aaronson et al. (22). The former comprises 36 items evaluating eight health domains QoL (i.e., physical functioning, role functioning, bodily pain, general health, vitality, social functioning, role emotional and mental health) with a score ranging from 0 to 100 with higher values indicating a better QoL. The latter focuses on five functional domains (i.e., physical, role, emotional, cognitive, and social), QoL and eight symptom-related dimensions (i.e., fatigue, nausea and vomiting, pain, dyspnea, insomnia, loss of appetite, constipation, diarrhea, and financial difficulties) with each item scored on a scale from 0 to 100. Higher values in the functional domains and QoL indicate better well-being, whereas higher values in the symptom scales reflect a greater symptom burden.

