#### Secondary analysis

2.12.2

The data obtained from the clinical questionnaires will be compared using parametric (e.g., ANOVA) or non-parametric (Friedman test) tests, as appropriate. The data obtained through gait analysis at *T_2_*will be compared with those at *T_3_*using parametric (e.g., t-test for paired samples) or non-parametric tests (e.g., Wilcoxon signed-rank test), according to the data characteristics and distribution.

The significance p level will be 0.05, and corrections will be executed in case of multiple comparisons among groups of data.

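### The 7-point TESS-LL responder rule cannot be met from a pre-operative score of 93 or more, and baseline TESS-LL is both part of the label and a candidate predictor of it, which biases the predictor analysis

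*Protocol article*

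**What the plan says.** - **Endpoint (2.10.1).** "The primary endpoint of the study will be the improvement of TESS-LL score between" T0 and T3. T0 falls in the week before surgery and T3 within 90 days after it (Figure 1).
- **Responder label (2.12.1).** The primary endpoint is also used to "classify the patients as responders (a change in TESS-LL score greater than 7 points) or non-responders". The article gives no derivation of the 7 points.
- **Predictor screen (2.12.1).** "baseline clinical data that will be significantly different between responders and non-responders will be adopted as inputs for multivariate logistic regression models", in order to look for predictors of recovery.
- **Scale (2.6).** TESS-LL is listed among the data collected at baseline. "The final score ranges from 0% to 100% with higher values indicating better function".
- **Level (2.12.2).** "The significance p level will be 0.05". Sidedness is not stated.

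The article has no rule for patients near the top of the scale and does not exclude baseline TESS-LL from the screen.

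**The concern.** Two features of the rule act in the same direction.

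The first is the ceiling. A gain of more than 7 points needs room above the starting score, and patients who start near 100 do not have it. They are non-responders by construction, whatever the rehabilitation achieves.

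The second is coupling. The label is built from T3 minus T0, and T0 is then tested as a predictor of the label. Measurement error in T0, and any T0-T3 correlation below 1, push T0 and the change in opposite directions. A low T0 then tends to go with response even when it carries no information about the effect of rehabilitation.

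At stake is the interpretation of the predictor analysis. The Discussion and Conclusion expect prognostic factors that will guide personalised rehabilitation. A finding that patients with low pre-operative function recover better could come partly or wholly from the definition.

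**Working it through.** **Figures in the plan.** The 7-point threshold has no stated derivation and the sample of 50 rests on case load (2.5), so there is no planned figure to reproduce. From the article: threshold above 7, scale 0 to 100, n = 50, level 0.05 (taken as two-sided). Assumed, because the article gives none: mean and SD of T0, reliability, T0-T3 correlation r, and mean change.

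**Step 1, ceiling (no assumption needed).** Response requires T3 − T0 > 7 with T3 ≤ 100, so T0 < 93. On the scoring described in 2.6 (30 items, 0 to 5) the step is 100/150 = 0.67. The highest T0 that can still respond is 92.67 (100 − 92.67 = 7.33); the next value, 93.33, leaves only 6.67.

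**Step 2, share of patients at T0 ≥ 93 (assumed distributions).** The result depends on how a normal curve is fitted to a bounded scale.

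| T0 mean/SD | Normal, excess piled at 100 | Normal truncated to 0–100 |
|---|---|---|
| 70/20 | 13% | 6% |
| 75/18 | 16% | 8% |
| 80/15 | 19% | 11% |
| 85/12 | 25% | 16% |

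Of 50 patients, that is about 6 to 13 in the first column and 3 to 8 in the second.

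**Step 3, coupling.** With equal SDs at T0 and T3, corr(T0, T3 − T0) = −√((1 − r)/2). This gives −0.59, −0.50, −0.39 and −0.22 for r = 0.3, 0.5, 0.7 and 0.9.

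**Step 4, chance that T0 passes the screen.** Simulated trials of 50, scores capped at 0 and 100, Mann-Whitney test of T0 between responders and non-responders.

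- *Mean T0 80, mean T3 78, SD 15.* T0 is significant in about 95%, 87%, 66% and 16% of trials at r = 0.3, 0.5, 0.7 and 0.9. Without the cap, the first three are 91%, 76% and 48%.
- *Same, but mean T3 15 points below T0.* About 42% at r = 0.5, roughly 10% at r = 0.7 and about 0% at r = 0.9, because few patients respond. The r = 0.7 figure moves by several points with the handling of trials that have very few responders.
- *True change unrelated to true T0* (change SD 15, reliability 0.8 to 1.0, mean change −10 to +7). This setting isolates the artefact. T0 is significant in 4–28% of trials at T0 60/20, 6–60% at 75/18 and 17–91% at 85/15. Of the significant results, 82–100% have the higher T0 in non-responders.
- *Same, with neither cap nor measurement error.* About 4–7%, close to nominal. The excess in the previous line therefore comes from the ceiling and from error in T0.

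**The case against.** **The bias may be small.** This stands as a limit on the claim. A reader might infer that the study will report baseline TESS-LL as a predictor. The documents do not support that: with low T0 scores and little measurement error, or with a high T0-T3 correlation and a large mean loss, the chance is near or below 5%.

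**Equal SDs with r below 1 already build in a negative link between T0 and change,** so the first simulation cannot separate artefact from a real tendency of low scorers to gain more. This is correct. The third setting removes the link, and it still shows rates well above 5% when T0 lies near the ceiling.

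**The rule says a change, without a sign.** A reader might infer that a loss of more than 7 points also makes a responder. Section 2.12.1 classifies on the primary endpoint, and 2.10.1 defines that endpoint as an improvement, so the direction is settled by cross-reference. Only the wording needs tidying.

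**A patient fully restored to the pre-operative level is a non-responder.** This is true, but at every T0: the change is 0 from 50 as from 95. It concerns the choice of a pre-operative reference and is separate from the ceiling.

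**The analysis is exploratory and added to the primary test.** Section 2.5 does call the results exploratory. That lowers the weight of the point but does not remove a bias with a known direction.

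**Conclusion.** The point holds as a bias of known direction and unknown size. That no patient with T0 of 93 or more can respond is plain arithmetic from the article's own scale and threshold. That T0 TESS-LL sits in both the label and the candidate list follows from 2.6, 2.10.1 and 2.12.1 read together. How many patients the ceiling affects, and how often T0 would pass the screen, rest on assumed inputs: 6–25% of patients across the four distributions in the table, and a screening rate from about nominal or below to over 90%. As written, a significant result for baseline TESS-LL could not be read as evidence about recovery. The Wilcoxon comparison of T0 with T3 uses the full scores and is untouched. The change is worth making, but the point does not threaten the primary analysis.

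**What to change.** 1. Make the main predictor analysis a linear model of T3 TESS-LL as a continuous outcome, with T0 TESS-LL forced into every model as an adjustment term and not interpreted as a predictor of recovery. With T0 in the model, the coefficients of the other predictors are the same whether the outcome is T3 or T3 − T0.
2. If the responder label is kept as a descriptive summary, write it as an improvement of more than 7 points, report how many patients have T0 of 93 or more, and exclude T0 TESS-LL from the candidate predictors of that label.

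Two other labels may seem attractive but repeat the fault. A gain of more than 7 from T2 to T3 has the same ceiling and coupling, now with T2. A recovered label (T3 no more than 7 points below T0) again contains T0: with the 80/78, SD 15 inputs, T0 differed significantly by that label in 87%, 65% and 34% of simulated trials at r = 0.3, 0.5 and 0.7.

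The cost is a change of analysis text. TESS-LL is already collected at T0 and T3, so no new data are needed. The small downside is that the predictor result is no longer expressed as odds of being a responder. T3 itself remains capped at 100, so the model's residuals should be checked.
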